### Sample size calculation

The primary endpoint will be the global health status/QoL scale (questions 29 and 30 of the EORTC-QLQ-C30)^31^ at 6 months post baseline. Assuming an SD of 21 points for the global health status/QoL scale and a mean difference of 7 or more points on the global health status/QoL scale between the groups is of clinical/practical importance (a ‘small’ standardised effect size of 0.33). With no allowance for clustering; for the PET versus surgery DESI comparison with 190 eligible women per group we will have a 90% power of detecting this difference or more as statistically significant between the groups at the 5% two-sided level. If we assume an intraclass correlation of 0.03 then allowing for the clustered RCT design we will need to recruit 10 women, eligible for using the decision aids, per cluster (ie, 50 clusters × 10 women), 500 in total (this assumes a design effect of 1.3). With a 20% loss to follow-up by 6 months we need to recruit 13 women per cluster (50 clusters × 13 women) or 650 in total (325 per group).

### Randomisation

Randomisation is at breast unit level, stratified by high and low PET and chemotherapy rates. It was therefore not possible to blind the investigators or the study sites to the allocation of participants. Data for this stratification have been derived from the wider cohort study which has collected data on treatment rates for both PET versus surgery/AET and chemotherapy versus no chemotherapy.

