### Objectives

The objectives are:To assess the effectiveness of the implementation of DESIs^26 27^ in clinical practice in terms of improving patient QoL, decision quality (integrating knowledge, attitudes and decision made), coping and illness representations, and reducing decision regret, thus indicating improved informed decision making.To determine if how, or to what extent, the clinical outcomes management algorithm impacts on clinical decision making among clinicians (change in PET/surgery rates and chemotherapy rates).To determine whether the DESIs are effective in improving short, medium and long-term cancer outcomes in this age group of women (treatment morbidity and overall and disease-specific survival).To assess the utility and uptake of the DESIs from the perspective of both clinicians and patients by undertaking a formal process evaluation.

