### Data analysis

The statistical analyses will be performed on an intention-to-treat basis comparing the DESI and control groups. All statistical exploratory tests will be two tailed with p=0.05. Baseline demographics (eg, age), physical measurements and health-related QoL data will be assessed for comparability between the treatment groups. A marginal generalised linear model (GLM), with coefficients estimated using generalised estimating equations (GEE) with robust SEs and an exchangeable autocorrelation matrix in STATA will be used to analyse the outcomes and allow for the clustered nature of the data. The exchangeable correlation structure corresponds to an equal correlation model, meaning that the correlations of the outcomes with a cluster, that is, breast centres, are the same. For continuous outcomes, such as mean global health status/QoL score (questions 29+30 of EORTC QLQ-C30^31^) at 6 months postdiagnosis/consent intervention, knowledge score and preference for treatment score, an identity link with a normal distribution for the outcome will be used. Estimates for the treatment group coefficient from this regression model will be reported along with their associated 95% CI. In the event of differences between the intervention and control groups with respect to baseline demographic, physical and health-related QoL measurements, then these covariates will be used in the GLM to adjust the treatment effect for these variables. The adjusted regression coefficient estimate for the treatment group parameter along with its 95% CI will then be reported.

For the other secondary outcomes, at 6 weeks and 6 months, such as the other dimensions of the EORTC QLQ C30,^31^ the EORTC QLQ-BR23^36^ and EORTC QLQ-ELD14,^37^ the mean QoL dimension scores will be compared between the intervention and control groups using similar models.

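### Breast units are randomised within PET- and chemotherapy-rate strata, but the stated GEE model has no stratum terms, so precision is lost wherever the strata predict the outcome

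*Protocol article*

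**What the plan says.** The Randomisation section gives the design: "Randomisation is at breast unit level, stratified by high and low PET and chemotherapy rates". The stratum information already exists for the units: "Data for this stratification have been derived from the wider cohort study which has collected data on treatment rates".

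The Data analysis section names a marginal model, described in these words: "with coefficients estimated using generalised estimating equations (GEE) with robust SEs and an exchangeable autocorrelation matrix in STATA will be used to analyse the outcomes". It reports the treatment-group coefficient. For continuous outcomes, "an identity link with a normal distribution for the outcome will be used". No link is given for binary outcomes.

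Covariates enter under one rule only. Its trigger reads: "In the event of differences between the intervention and control groups with respect to baseline demographic, physical and health-related QoL measurements". The consequence of that trigger is worded as: "then these covariates will be used in the GLM to adjust the treatment effect for these variables". Unit treatment rates are not among the variables it lists. The exploratory subgroup models use the same GEE structure and add no stratum terms.

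The second objective concerns the effect of the algorithm on clinical decisions, measured as "change in PET/surgery rates and chemotherapy rates".

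**The concern.** Stratified allocation forces the arms to have nearly the same mix of strata. Differences between strata therefore drop out of the true sampling error of the arm comparison. A model without stratum terms still counts those differences as residual variation between units. The sandwich estimator does not correct this, because it treats units as independent draws and is unaware of the restricted allocation. The result is intervals that are too wide and tests that run below their nominal level.

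The size depends on how well the strata predict the outcome. For treatment rates the link is built in, since the strata were formed from those same rates, and the Introduction reports wide variation between UK units (fourfold for PET; 6% to 60% for chemotherapy in high-risk women). For global quality of life the link is an open question.

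**Working it through.** **The plan's own figure.** Inputs from the Sample size calculation section: SD 21, difference 7, 90% power, two-sided 5%, ICC 0.03, 10 women per unit, 50 units.

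- Per group without clustering: 2 × (1.96 + 1.2816)² × 21²/7² = 189.1, so 190, as stated.
- Design effect: 1 + 9 × 0.03 = 1.27, stated as 1.3. Then 380 × 1.3 = 494, rounded to 50 × 10 = 500.
- Loss to follow-up: 10/0.8 = 12.5, so 13 per unit and 650 in total.

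The sample size reproduces. It takes no credit for stratification.

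**Primary outcome.** In units of the total variance, a unit mean has variance V = ICC + (1 − ICC)/m = 0.03 + 0.97/10 = 0.127. With 25 units per arm, the SE without strata is 21 × √(2 × 0.127/25) = 2.117. If the strata explain a share s of between-unit variance, that SE is too wide by the factor r = √[V/(V − s × ICC)], and the true SE is 2.117/r. The article does not give s, so a range is shown.

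- True test size = 2[1 − Φ(1.96r)]
- Power without strata = Φ[(7 − 1.96 × 2.117)/(2.117/r)]
- Power with strata = Φ[7/(2.117/r) − 1.96]

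For s = 0.5: r = √(0.127/0.112) = 1.065 and the true SE is 1.988. Power without strata is Φ(2.851/1.988) = Φ(1.434) = 92.4%. Power with strata is Φ(3.521 − 1.96) = Φ(1.561) = 94.1%.

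| s (assumed) | SE excess | True test size | Power without strata | Power with strata |
|---|---|---|---|---|
| 0 | 0% | 0.050 | 91.1% | 91.1% |
| 0.25 | 3.1% | 0.043 | 91.8% | 92.6% |
| 0.5 | 6.5% | 0.037 | 92.4% | 94.1% |
| 1 (bound) | 14.4% | 0.025 | 93.8% | 96.6% |

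**Treatment rates.** The article gives no ICC or stratum rates, so these were assumed and simulated: 50 units in four strata, balanced within strata, 10 women per unit, a between-unit SD of 5 percentage points within strata, identity link (risk difference), cluster-robust SE, 5,000 runs. The excess is the mean reported SE over the actual SD of the estimate.

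| Outcome, assumed low/high stratum rates | SE excess without strata | True test size |
|---|---|---|
| PET 20/30% | 5% | 0.043 |
| PET 15/35% | 22% | 0.018 |
| PET 10/40% | 43% | 0.005 |
| Chemotherapy 8/20% | 11% | 0.030 |
| Chemotherapy 15/45% | 40% | 0.007 |
| Chemotherapy 6/60% (extreme) | 116% | below 0.001 |

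**Sensitivity of the treatment-rate figures.** The formula for r shows how quickly the excess shrinks. Take an assumed ICC of 0.10. A median split on a normally distributed true unit rate explains 2/π, about 64%, of between-unit variance.

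- 10 women, s = 0.64: √(0.190/0.126) = 1.23, a 23% excess.
- 10 women, s = 0.32: √(0.190/0.158) = 1.10, 10%.
- 3 women, s = 0.64: √(0.400/0.336) = 1.09, 9%.
- 3 women, s = 0.32: √(0.400/0.368) = 1.04, 4%.

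**Small-sample behaviour.** The same simulation set-up was run for the quality-of-life score (8,000 runs, uncorrected robust SE, critical value 1.96).

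| s | SE/actual SD without strata | Test size without strata | SE/actual SD with strata | Test size with strata |
|---|---|---|---|---|
| 0 | 0.995 | 0.057 | 0.962 | 0.064 |
| 0.25 | 1.003 | 0.055 | 0.941 | 0.071 |
| 0.5 | 1.053 | 0.041 | 0.958 | 0.064 |
| 1 | 1.118 | 0.031 | 0.947 | 0.069 |

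With about 50 units the uncorrected robust SE is slightly too small. At s = 0.25 this roughly cancels the conservatism. Across all simulated outcomes the strata-adjusted model gave SEs 0.94 to 0.97 of the true SD and test sizes of 0.06 to 0.07.

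**The case against.** The strongest reply is that the article is silent on the strata rather than opposed to them. Its covariate rule concerns patient measurements, so it neither admits nor forbids unit-level factors, and naming stratification factors is often left to an analysis plan, which is not shown here. That stands in part: such a plan may already include them. But the article fixes a model and a rule for what enters it, and following that text leaves the strata out.

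Second, the larger figures concern outcomes whose analysis the article barely describes. No binary link is stated, and on a logit scale adjustment changes what the coefficient estimates, so SEs with and without strata could not be compared directly. Nor is 10 women per unit given for the chemotherapy decision, which arises in a different group of women. Strata formed from estimated cohort rates will also predict less well than true rates. All of this stands and is why the treatment-rate figure is a range resting on assumptions.

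Third, nothing in the article shows that the strata predict quality of life, and the planned power does not depend on their doing so. This also stands.

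A reader might infer that the primary analysis is invalid or underpowered, or that its SEs are certainly too wide. The document supports none of these: the excess may be zero, and the stated power holds in every row of the primary-outcome table. A reader might also take the 6% to 60% span as the stratum contrast. It is the range across individual UK units, so the 116% row is an extreme and not an expectation.

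**Conclusion.** The point holds as a matter of efficiency. The model as written does not reflect the stratified randomisation, and wherever the strata predict an outcome its SEs err on the wide side. It introduces no bias in the risk difference or mean difference, and the omission itself does not raise the false-positive rate.

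For PET/surgery and chemotherapy rates the loss is expected and could matter, at roughly 5–40% in the SE under moderate stratum contrasts. That rests on assumed stratum rates, 10 women per unit and the risk-difference scale. For the primary outcome it is modest: adding the strata would gain 0 to 2.8 percentage points of power (96.6 − 93.8 at the bound), starting from a level already above 90%.

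**What to change.** Prespecify the PET-rate and chemotherapy-rate strata as fixed covariates in the primary and all secondary GEE models, regardless of observed baseline balance. If the unseen analysis plan already does so, confirm it.

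Pair this with a small-sample correction to the robust SEs suited to about 50 clusters, for example a bias-corrected sandwich with a t reference distribution. Adding the strata alone would replace a mildly conservative test with a mildly liberal one.

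For binary treatment-rate outcomes, state the link and report the effect as a marginal risk difference, so that adjustment does not change the estimand. Each unit's pre-randomisation cohort rate may be used as an optional continuous covariate for these outcomes.

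The cost is a sentence or so of analysis wording. The stratum data are already held for the randomised units, and no new data are needed.

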### Control arm

Usual standard practice for older women (>70 years) diagnosed with breast cancer with no change to normal treatment decision-making practice.

### Intervention arm

Usual standard practice for older women (>70 years) diagnosed with breast cancer plus optional clinician and patient access to the package of DESIs which will have been made available to these units to adopt as their standard of care.

In the run into the trial period (June–December 2015), clinical teams (clinicians, research and breast nurses) from the participating sites attended a training event to enhance concordance with the study protocol (control group) and provide additional training on shared decision making and the use of the DESIs (intervention group). This comprised a 2-hour practical workshop which consisted of presentations, demonstrations and discussion based on the MAGIC programme.^46^

### Recruitment

Potentially eligible women are identified by clinicians (breast surgeons, medical oncologists and specialist breast nurses) and research nursing staff within multidisciplinary teams of the study sites. Study packs are being given to eligible patients either following their clinical consultation where either PET or surgery/AET options or chemotherapy versus no chemotherapy options are discussed. Monthly study newsletters are sent to all participating sites to provide feedback to staff in order to maintain interest and recruitment to the study. Any modifications to the original study protocol will be discussed with the data monitoring and ethics committee and approvals sought from the funder and the ethics committee. Recruitment for the trial has now commenced and 750 women have been recruited over the 53 participating sites.

### Data analysis

The statistical analyses will be performed on an intention-to-treat basis comparing the DESI and control groups. All statistical exploratory tests will be two tailed with p=0.05. Baseline demographics (eg, age), physical measurements and health-related QoL data will be assessed for comparability between the treatment groups. A marginal generalised linear model (GLM), with coefficients estimated using generalised estimating equations (GEE) with robust SEs and an exchangeable autocorrelation matrix in STATA will be used to analyse the outcomes and allow for the clustered nature of the data. The exchangeable correlation structure corresponds to an equal correlation model, meaning that the correlations of the outcomes with a cluster, that is, breast centres, are the same. For continuous outcomes, such as mean global health status/QoL score (questions 29+30 of EORTC QLQ-C30^31^) at 6 months postdiagnosis/consent intervention, knowledge score and preference for treatment score, an identity link with a normal distribution for the outcome will be used. Estimates for the treatment group coefficient from this regression model will be reported along with their associated 95% CI. In the event of differences between the intervention and control groups with respect to baseline demographic, physical and health-related QoL measurements, then these covariates will be used in the GLM to adjust the treatment effect for these variables. The adjusted regression coefficient estimate for the treatment group parameter along with its 95% CI will then be reported.

For the other secondary outcomes, at 6 weeks and 6 months, such as the other dimensions of the EORTC QLQ C30,^31^ the EORTC QLQ-BR23^36^ and EORTC QLQ-ELD14,^37^ the mean QoL dimension scores will be compared between the intervention and control groups using similar models.

A series of exploratory subgroup analyses using a marginal GLM with coefficients estimated using GEE with robust SEs and an exchangeable autocorrelation matrix, with the primary outcome the mean global health status/QoL score (questions 29+30 of EORTC QLQ-C30^31^) at 6-month postdiagnosis/consent randomisation as the response will be carried out. An interaction statistical test between the randomised intervention group and subgroup to directly examine the strength of evidence for the treatment difference between the treatment groups (intervention vs control) varying between subgroups will be undertaken. Age subgroup (75–79, 80–84, 85–89 and 90+ years) and comorbidity levels (based on the modified Charlson comorbidity score^32^) will be the only a priori defined subgroups to be considered for interaction test. Subgroup analysis will be performed regardless of the statistical significance on the overall intervention effect (intervention vs control).

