In addition, specific questionnaires relating to patient choice and decision making will be administered. These will apply to all women offered a choice of either PET and surgery/AET or chemotherapy versus no chemotherapy and are administered in relation to the time of their treatment choice. Secondary outcome measures here include decision regret (Decision Regret Scale,^39^ shared decision making (CollaboRATE^40^), patient anxiety (Spielberger short-form state scale of the State-Trait Anxiety Inventory,^41^ knowledge and preference (knowledge, readiness to decide and preference measure^42 43^), illness perceptions (Brief Illness Perceptions Questionnaire^44^) and Coping (brief COPE, Coping Orientation to Problems Experienced)^45^). Original data collected are entered and kept on file within each of the study sites. These data are entered electronically and stored securely onto password-protected databases within local databases and the main trial office. All records that contain names or other personal identifiers, such as locator forms and informed consent forms, are stored separately from study records identified by code number. Only the study steering and DMC have access to the full trial data set. Errors, discrepancies or missing data are captured by the computer programme and the study data manager checks and subsequently follows this up with participating sites.

The timescales for each of these are shown in table 1.

**Table 1 d35e986:** Questionnaire schedule

Standard age gap questionnaires	Baseline	6 weeks	6 months	12 months	18/24 months	Long term
IADL	*					
ADL	*					
MMSE	*					
ECOG performance status	*					
Subjective global assessment	*					
Comorbidity	*					
EQ5D	*	*	*	*	*	
QoL (EORTC-QLQ C30, QLQ-BR23 and QLQ-ELD14)	*	*	*	*	*	
Decision quality	*	*				
RECIST if PET	*	*	*	*	*	
Registry data access						*
Tissue access	*					*
Tumour details	*					
Treatment details	*	*	*	*	*	
Adverse events	*	*	*	*	*

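### Baseline adjustment depends on observed imbalance, and neither the unadjusted nor the adjusted estimate is named primary; a fixed covariate set would be better

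*Protocol article*

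**What the plan says.** The Data analysis section of the protocol article describes a GEE model with an identity link for the 6-month global health status/QoL score, clustered by breast unit. It names no covariates, and its treatment coefficient with 95% CI is reported in every case. Baseline data are then checked for comparability, and the rule follows: "In the event of differences between the intervention and control groups with respect to baseline demographic, physical and health-related QoL measurements, then these covariates" are put in the model. After that, "The adjusted regression coefficient estimate for the treatment group parameter along with its 95% CI will then be reported".

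The section does not define a difference, gives no closed list of covariates, and does not rank the two estimates.

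Three other places bear on this:

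- Table 1 schedules "QoL (EORTC-QLQ C30, QLQ-BR23 and QLQ-ELD14" at baseline as well as at follow-up, so the baseline value of the primary measure is available. Age and the Charlson index are also recorded at diagnosis (Data collection and outcomes).
- The Randomisation section stratifies units by their PET and chemotherapy rates. The analysis model does not mention these factors.
- The Recruitment section has study packs handed out after the consultation in which treatment options are discussed, at units that know their allocation.

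**The concern.** A covariate improves a treatment estimate because it predicts the outcome, whether or not the arms happen to differ on it. The baseline score on the primary scale is the natural candidate, yet under this rule it enters the effect model only if an imbalance is seen. When none is seen, the precision it offers is lost.

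When one is seen, the report holds two estimates of the primary effect. The covariates in the second were chosen after looking at the data, and nothing says which estimate is the result.

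The design makes this more than a formality. Women are identified by staff at units that know their arm, and the article itself lists recruitment-related selection bias as a possible limitation. Some real imbalance is therefore plausible, and decisions about adjustment would be made after it had appeared. At stake are precision and a clear primary estimate.

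**Working it through.** **Inputs from the Sample size calculation section.** SD 21 ("Assuming an SD of 21 points for the global health status/QoL scale"); target difference 7 ("a mean difference of 7 or more points on the global health status/QoL scale"); two-sided 5% ("as statistically significant between the groups at the 5% two-sided level"); power 90% ("we will have a 90% power of detecting this difference"); "with 190 eligible women per group" before clustering; ICC 0.03; 50 clusters of 10; design effect 1.3; 20% loss.

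**Assumed.** The correlation r between the baseline and 6-month scores, 0.3 to 0.7. The article gives no value.

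**1. Reproduce the plan's figures.**

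- Per group: 2 × (1.960 + 1.282)² × (21/7)² = 189.1, so 190. This agrees.
- Design effect: 1 + (10 − 1) × 0.03 = 1.27, stated as 1.3.
- 2 × 190 × 1.3 = 494, rounded to 50 × 10 = 500.
- Loss: 10/0.8 = 12.5, rounded up to 13 per cluster; 13 × 50 = 650.

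The calculation is sound and assumes no baseline adjustment.

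**2. Power with and without fixed adjustment.**

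- Effective n per arm = 250/1.3 = 192.3.
- Unadjusted SE = 21 × √(2/192.3) = 2.142.
- Adjusted SE = 2.142 × √(1 − r²).
- Power = Φ(7/SE − 1.96).

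| r | SE | Power |
|---|---|---|
| unadjusted | 2.142 | 90.5% |
| 0.3 | 2.043 | 92.9% |
| 0.4 | 1.963 | 94.6% |
| 0.5 | 1.855 | 96.5% |
| 0.6 | 1.713 | 98.3% |
| 0.7 | 1.529 | 99.6% |

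**3. What the conditional rule delivers.** The article sets no threshold, so a baseline difference with p < 0.05 was assumed as the trigger. The simulation analysed cluster means in 25 units of 10 per arm. ICC was 0.03 for both scores, r was the same at cluster and individual level, and randomisation was sound. There were 50,000 runs under the 7-point difference and 100,000 under the null.

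| r | Power, never adjust | Power, adjust if triggered | Power, always adjust | Type I error, adjust if triggered | Type I error, either estimate may count |
|---|---|---|---|---|---|
| 0.3 | 90.1% | 90.2% | 92.0% | 4.7% | 6.4% |
| 0.5 | 90.0% | 90.7% | 95.9% | 4.4% | 7.3% |
| 0.6 | 90.0% | 91.1% | 97.9% | 4.0% | 7.7% |
| 0.7 | 90.2% | 91.6% | 99.5% | 3.6% | 8.4% |

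The trigger fires in about 5% of trials, so it recovers little. At r = 0.5 it gains 0.7 of the 5.9 points available.

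**4. What the last column assumes.** It takes both estimates to be at hand in every trial, with the significant one free to be called the finding. If the adjusted estimate existed only after a strict p < 0.05 trigger on this one covariate, the free choice would add little. Under the null the adjusted test is independent of the baseline difference. The extra error is therefore at most 0.05 × 0.05 = 0.25 percentage points, for a total of at most 5.25%. The 6–8% figure applies because the article leaves the criterion for a difference undefined, so both estimates may well be available.

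**The case against.** **The unadjusted model is fixed and always reported.** On a natural reading the adjusted estimate is an addition, and a sample size built on the raw SD of 21 fits an unadjusted primary analysis. This largely stands. The data decide whether an adjusted model exists and what it contains; they do not displace the unadjusted one. What remains is that neither is designated primary. Even if the unadjusted estimate were named, the loss of precision would remain.

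**The threshold and covariate list may be in an analysis plan that is not shown.** That is fair, and their absence is not the point. The trigger itself is stated, and a plan that follows the article would inherit it.

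**Power already meets 90%.** This is correct. The precision is a missed gain, not a shortfall, and its size depends on an assumed correlation.

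**Imbalance from biased recruitment is a reason to adjust.** That is also correct in a cluster trial of this kind. It favours adjusting for the main prognostic factors in every case; it does not favour waiting to see which ones differ.

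**Stronger readings to resist.** A reader might infer that the rule inflates false positives. Applied mechanically it does the opposite (3.6–4.7%); inflation needs freedom to choose between estimates, which the article neither grants nor rules out. A reader might also calculate how likely it is that at least one of many baseline variables is flagged at 5%. The article states no baseline tests, threshold or number of variables. The scales overlap, so independence is implausible, and such a figure is not an error rate for the treatment effect.

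**Conclusion.** The point holds as a matter of analysis choice. The article makes adjustment depend on observed baseline differences and leaves the primary estimate unnamed when two exist.

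The main cost is precision: about 90.5% power unadjusted, against 94.6–98.3% with fixed adjustment at r = 0.4–0.6, and only about 90–92% under the trigger across r = 0.3–0.7. The second cost is an open choice of estimate, worth a type I error of about 6–8% if both are available and either may count.

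These figures rest on the assumed r, an assumed p < 0.05 trigger, equal clusters of 10, ICC 0.03 for both scores and sound randomisation. The sample size and its 90% power stand as stated. The change should be made, but the plan is not invalid without it.

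**What to change.** Delete the trigger and name one primary GEE model whose covariates are fixed regardless of balance:

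- the stratification factors (unit PET rate and unit chemotherapy rate, each high or low);
- age;
- Charlson comorbidity;
- baseline QLQ-C30 global score.

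Label the unadjusted estimate as supportive.

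First confirm when baseline QoL is completed relative to use of the decision support. Women receive study packs after the treatment consultation, at units that know their allocation, so in intervention units the baseline score could follow exposure, and adjusting for it could remove part of the effect. If it can follow exposure, show the result with and without baseline QoL. Age and comorbidity do not raise this problem.

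The cost is a change of wording, a stated way of handling missing baseline values, and one extra sensitivity analysis. The individual covariates are already collected, and the stratification factors are known from randomisation.

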### Eligibility criteria

#### Inclusion criteria

female;aged over 70 years at the time of diagnosis of cancer;primary operable (tumour, node, metastasis (TNM) categories V7: T1, T2, T3, N0, N1, M0), ER-positive invasive breast cancer (core biopsy or diagnostic incision biopsy);ability to give informed consent and to read English.

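### The pre-specified age subgroups begin at 75 although women over 70 are eligible, so as written women under 75 have no category in the exploratory age interaction test

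*Protocol article*

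**What the plan says.** The inclusion criteria set the age limit as "aged over 70 years at the time of diagnosis of cancer" and state no upper limit. The arm descriptions use the same population. The control arm reads "Usual standard practice for older women (>70 years) diagnosed with breast cancer with no change to normal treatment decision-making practice", and the intervention arm reads "Usual standard practice for older women (>70 years) diagnosed with breast cancer plus optional clinician and patient access to the package of DESIs".

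The Data analysis section then announces "A series of exploratory subgroup analyses using a marginal GLM", with the 6-month global health status/QoL score as the response and a test of interaction between randomised arm and subgroup. The age factor and its companion are "Age subgroup (75–79, 80–84, 85–89 and 90+ years) and comorbidity levels", and these two "will be the only a priori defined subgroups to be considered for interaction test". The article gives no other age cut-points for analysis.

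**The concern.** The cut-points are stated outright, so this is not a detail left to a fuller document. Followed literally, they give no category to any eligible woman who has not reached 75. A record with a missing factor level drops out of a model that contains that factor and its interaction with arm. One of only two pre-specified interaction tests would then describe women aged 75 and over rather than the randomised population.

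If a youngest or reference band was intended, the article does not say so. Adding it after outcomes have been seen would leave that band open to the charge of being post hoc against the published protocol.

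**Working it through.** **Inputs.** Age over 70 (Inclusion criteria, Control arm, Intervention arm); bands 75–79, 80–84, 85–89 and 90+ (Data analysis); SD 21, difference 7, 90% power, 5% two-sided, intraclass correlation 0.03, design effect 1.3, 20% loss, 50 clusters (Sample size calculation); 750 women already recruited (Recruitment).

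**1. The plan's own sample size.** This is needed only as a denominator.

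- Per group before clustering: 2 × (1.960 + 1.282)² × (21/7)² ≈ 189 by the normal approximation, and 190 with the t correction. This agrees with the stated 190.
- Clustering: 380 × 1.3 = 494, stated as 50 × 10 = 500. (The exact design effect for 10 per cluster is 1 + 9 × 0.03 = 1.27, giving 483.)
- Loss to follow-up: 10 / 0.8 = 12.5, rounded up to 13 per cluster; 13 × 50 = 650, as stated.
- Expected with 6-month data: 650 × 0.8 = 520. The figure of 500 is the requirement before loss and before rounding up per cluster, so 520 is the right denominator for women with an outcome.

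The sample size reproduces and does not itself bear on the age bands.

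**2. Coverage of the bands.** Each whole-year age from 70 upward was compared with the list.

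| Age at diagnosis | Eligible? | Listed band |
|---|---|---|
| 70 | only if past the 70th birthday counts as over 70 | none |
| 71, 72, 73, 74 | yes | none |
| 75–79 | yes | 75–79 |
| 80–84 | yes | 80–84 |
| 85–89 | yes | 85–89 |
| 90 and over | yes | 90+ |

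Every age from 75 upward is covered and none below it.

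**3. Effect on the test.** Four bands give an interaction test with 4 − 1 = 3 degrees of freedom, fitted only to women aged 75 or more. One further band gives 5 − 1 = 4 degrees of freedom, fitted to all eligible women with an outcome.

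**4. How many women.** The article gives no age distribution, so the share under 75 is an assumption, shown over a wide range.

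| Assumed share under 75 | of 650 planned | of 520 with 6-month data | left in the age model | of 750 recruited |
|---|---|---|---|---|
| 10% | 65 | 52 | 468 | 75 |
| 20% | 130 | 104 | 416 | 150 |
| 30% | 195 | 156 | 364 | 225 |
| 40% | 260 | 208 | 312 | 300 |
| 50% | 325 | 260 | 260 | 375 |

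**The case against.** The strongest reply has three parts.

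- **No exclusion is stated.** The article has no rule removing women under 75, and the list may simply have lost its youngest or reference band in drafting. A reader might infer a deliberate restriction to women aged 75 and over; nothing in the article supports that. What stands is that the list is incomplete as written and that no text repairs it.
- **The reach is small.** The subgroup analyses are labelled exploratory, the primary analysis is by intention to treat without age bands, and the sample size is not built on an interaction. This stands in full.
- **The importance of the missing group is easily overstated.** A reader might infer that women under 75 are those whose treatment choice is most likely to differ. The article does not support this as a general statement. For primary endocrine therapy versus surgery, the Introduction places the complex trade-offs in women at raised surgical risk, and the algorithm for that decision is directed at frailer women. Only the chemotherapy decision is tied to fitter women, which gives the younger band some relevance there and no more.

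A reader might also expect the 90+ band to be so sparse that the test becomes unstable. That may prove true, but the article gives no age distribution from which to show it.

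**Conclusion.** The point holds in a limited form. The listed age bands do not cover the eligible range, and women under 75 cannot enter the categorical age-by-arm interaction model as written. The mismatch is certain, because it follows from comparing the inclusion criterion with the list.

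The consequence is minor: one exploratory test is affected, and the primary comparison still includes every randomised woman over 70. It would be wrong to read this as a threat to the trial's main result. The number of women involved is unknown; the range in the table rests wholly on the assumed share of 10% to 50% and is not an estimate.

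**What to change.** In the subgroup paragraph of the Data analysis section, and in any analysis plan that repeats it, add a lowest band defined as over 70 and under 75. Do this before outcome data are analysed. This wording is safer than 71–74, which could still miss a woman aged 70 and some months if she counts as over 70.

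The cost is one line of text and one further degree of freedom in the interaction test, plus the approval route in the Recruitment section if the change counts as a protocol modification. Eligibility, sample size and the primary analysis do not change.

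Testing the interaction with age as a continuous variable over the full range is an optional supplement; a single linear term could miss a non-linear pattern, so it need not replace the bands. Merging the oldest bands is a matter of preference and not a correction.
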